### Standard procedures

In order to avoid interference with the trial intervention, perioperative anesthesia care (including induction and maintenance of general anesthesia, postoperative pain management, and fluid management) is performed by a relatively fixed anesthesia team according to clinical routine. The following approaches are suggested:
Adequate airway assessment is required in all patients, predicated on 12 predictors of a difficult airway, and when more than three predictors are present, consideration should be given to intubating the trachea with an awake endotracheal tube or with slow induction to preserve spontaneous breathing, establishing an airway and preparing adequate equipment, personnel, and drugs in advance (Attached Table 1: Predictors of Difficult Airway).Patients are routinely monitored after admission in the operating room, such as blood pressure, electrocardiogram, pulse oxygen saturation, BIS, and urine volume. Invasive arterial pressure was monitored by radial or dorsalis pedis artery puncture under local anesthesia.For patients without anticipated difficult airway, rapid sequence induction was used for anesthesia induction: midazolam 0.05 mg/kg is given 15 min before induction, anesthesia is induced with etomidate, sufentanil, rocuronium, or cisatracurium, and mechanical ventilation was performed after tracheal intubation.Anesthesia is maintained with total intravenous anesthesia by using intravenous propofol and remifentanil.The maintenance of intraoperative circulation is actively managed based on surgery procedure and bleeding.Perform postoperative pain treatment to control a visual analogue scale (VAS) pain score < 3. Local incision anesthesia or neuraxial block should be performed.Encourage early mobilization, deep breathing exercises, and stimulation of cough in the postoperative period.

Data on the procedures applied will be recorded in detail and analyzed. All anesthesia and related treatment need to comply with clinical routines. Nasogastric tubes and intravenous catheters may be used according to surgery practice or guidelines. Urinary bladder catheter is usually not inserted according to the routine for this type of surgery in our hospital.

### Mechanical ventilation

The breathing settings for mechanical ventilation are as follows: using the pressure-control-volume compensation mode (PSC-VC) to set the driving pressure to 15 cmH_2_O. We used the lowest possible fraction of inspired oxygen (FiO_2_ ≥ 0.5) to maintain a peripheral oxyhemoglobin saturation measured (SpO_2_) > 92%. The compensated tidal volume is set to 7 ml/kg (PBW) and the respiratory rate to 12–15 breaths/min (targeting P_ET_CO_2_ maintenance at 35–45 cmH_2_O). Anesthetic complications were managed according to clinical guidelines. Pulmonary ventilation was recorded by EIT observation before induction of anesthesia and after extubation in each group.

### Intervention

After induction of anesthesia in all patients, PEEP was maintained at 5 cmH_2_O, mechanical ventilation was performed for 5 min, and baseline measurements of relevant parameters were performed in all patients. In the PEEP5 group, 5 cmH_2_O PEEP was maintained throughout the mechanical ventilation. Ventilator-driven alveolar recruitment maneuver (RM) is performed three times in both groups. In both groups, the first RM is performed at the moment of 5 min after intubation, the second RM is performed at the moment of establishment of pneumoperitoneum, and the third RM is at the moment before extubation. The ventilator-driven alveolar recruitment maneuver is performed as following steps [18] (Fig. 2):
In pressure control mode, the driving pressure is set to 15–20 cmH_2_O.Starting at a PEEP of 5 cmH_2_O and increasing in steps of 5 cmH_2_O, each increase was maintained for 30 s until it was increased to a PEEP of 20 cmH_2_O, with a inspiratory plateau pressure as high as 40 cmH_2_O. Maintain 5 breaths at PEEP = 20 cmH_2_O to the end.During the whole period of RM, *V*_*T*_ is 7 ml/kg, and I:E is 1:1.Ppeak < 55 cmH_2_O.A standardized fluid therapy regimen was used in all patients, and during RM, patients were given according to the protocol, along with vasopressors, to maintain MAP > 70 mmHg and minimize short-term hemodynamic suppression during RM.

**Fig. 2 Fig2:**
[figure not shown]
The ventilator-driven alveolar recruitment maneuver protocol. Ppeak, peak airway pressure; Pplat, plateau airway pressure; PEEP, positive end-expiratory pressure; *V*_*T*_, tidal volume normalized for adjusted body weight; I:E, ratio between inspiratory and expiratory time; RR, respiratory rate

The iPEEP group obtained iPEEP for this patient by following these steps (Fig. 3):
First RM1: At 5 min after intubation, the first RM is performed.Set airway peak pressure not to exceed 55 cmH_2_O.*V*_*T*_ to 7 ml/kg (adjusted body weight, ABW), respiratory rate 12–15 breaths/min, I: E to 1:1.Titration process: At the moment of establishment of pneumoperitoneum, we begin to titrate the iPEEP (Fig. 4). Setting initial PEEP to 5 cmH_2_O, increasing PEEP according to the gradient of 2 cmH_2_O every 3 min, calculating Cstat (according to the formula: Cstat = *V*_*T*_/Plat-PEEP). Gradually increasing PEEP, until the calculated Cstat shows a downward trend, set its previous PEEP (corresponding to PEEP for high Cstat) as the optimal iPEEP for this patient.The highest PEEP is limited to 20 cmH_2_O.After setting the iPEEP, the second RM2 is performed.Before extubation, the third RM3 is performed.

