**Methods:**

This study is a single-center, two-arm, prospective, randomized control trial. A total number of 80 obese patients with body mass index ≥ 32.5 kg/m^2^ scheduled for laparoscopic gastric volume reduction and at medium to high risk for PPCs will be enrolled. They will be randomly assigned to control group (PEEP5 group) and iPEEP group. A PEEP of 5 cmH_2_O will be used in PEEP5 group, whereas an individualized PEEP value determined by a Cstat-directed PEEP titration procedure will be applied in the iPEEP group. Standard lung-protective ventilation methods such as low tidal volumes (7 ml/kg, predicted body weight, PBW), a fraction of inspired oxygen ≥ 0.5, and recruitment maneuvers (RM) will be applied during and after operation in both groups. Primary endpoints will be postoperative atelectasis measured by chest electrical impedance tomography (EIT) and intraoperative oxygen index. Secondary endpoints will be serum IL-6, TNF-α, procalcitonin (PCT) kinetics during and after surgery, incidence of PPCs, organ dysfunction, length of in-hospital stay, and hospital expense.

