## Abbreviations

PPCs: Postoperative pulmonary complications
iPEEP: Individualized positive end-expiratory pressure
Cstat: Static lung compliance
FiO_2_: Inspiratory fraction of inspired oxygen
EIT: Electrical impedance tomography
PBW: Predicted body weight
RM: Recruitment maneuvers
*V*_*T*_: Tidal volume
CRF: Case report forms
ARISCAT: The Assess Respiratory Risk in Surgical Patients in Catalonia
BMI: Body mass index
COPD: Chronic obstructive pulmonary disease
VAS: Visual analogue scale
PSC-VC: Pressure-control-volume compensation mode
Pplat: Plateau airway pressure
Ppeak: Peak airway pressure
1:E: Ratio between inspiratory and expiratory time
PaO_2_: Partial pressure of arterial oxygen
PCT: Procalcitonin

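### The 7 ml/kg tidal volume is tied to predicted body weight in one place and adjusted body weight in another, and nothing reconciles the two

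*Protocol article*

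**What the plan says.** All of the statements are in the protocol article.

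- **Abstract, Methods:** "low tidal volumes (7 ml/kg, predicted body weight, PBW"), among the lung-protective measures that "will be applied during and after operation in both groups".
- **Mechanical ventilation:** "The compensated tidal volume is set to 7 ml/kg (PBW"). The sentence is not limited to one arm.
- **Intervention, recruitment maneuver (RM) steps, both groups:** tidal volume "is 7 ml/kg, and I:E is 1:1", with no weight basis. The maneuver is pressure-controlled: "In pressure control mode, the driving pressure is set to" 15–20 cmH2O.
- **Fig. 2 legend (RM):** "tidal volume normalized for adjusted body weight".
- **Steps for the iPEEP group, after Fig. 2:** tidal volume "to 7 ml/kg (adjusted body weight, ABW"), with a rate of 12–15 breaths/min and I:E of 1:1. This line comes after the first RM and the 55 cmH2O peak limit, and directly before the titration step.

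The Background cites 6–8 ml/kg PBW as the recommended range. Entry requires BMI of at least 32.5.

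**The concern.** The same number, 7 ml/kg, is attached to two different weights in current operative text. PBW depends on height and sex only, whereas an adjusted weight normally adds part of the excess weight. Under any such definition the two diverge in obese patients, and this trial enrols no others.

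The wording also falls unevenly. In the procedural text, ABW appears only in the steps for the iPEEP group. Staff who took that line as the setting to run from then on would ventilate the iPEEP arm with larger nominal tidal volumes than the control arm. Randomisation would still give a fair comparison of the two packages as delivered. However, a difference in oxygenation index or lung collapse area could no longer be put down to PEEP alone. It would also be a safety matter in a trial that presents low tidal volume as standard care in both groups.

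**Working it through.** **1. Which reading does the text favour?**

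| Feature of the iPEEP-group lines | Also in the RM description? | Also in the general settings? |
|---|---|---|
| Peak pressure limit 55 cmH2O | Yes, RM steps | No |
| I:E 1:1 | Yes, RM steps and Fig. 2 legend (ratio listed) | No |
| Tidal volume on ABW | Yes, Fig. 2 legend | No, PBW |
| Rate 12–15/min | Respiratory rate listed in Fig. 2 legend, no value | Yes |
| Position | Directly after the first RM | – |

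This pattern fits a setting for the RM, which is given to both groups. The rate adds little support to a running setting, because the Fig. 2 legend lists respiratory rate too. The points left in favour of a running setting are that the line stands only in the iPEEP steps and comes just before titration.

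**2. Size if it were a running setting.** The protocol states no figure to reproduce and gives neither weight formula, so these are assumptions:

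- PBW = 45.5 (women) or 50 (men) + 0.91 × (height in cm − 152.4)
- ABW = PBW + f × (actual weight − PBW), with f from 0.25 to 0.40
- women of 160 and 165 cm, men of 170 and 175 cm
- actual weight = BMI × (height in m)²

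Worked example, woman of 160 cm at BMI 32.5:

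- PBW = 45.5 + 0.91 × 7.6 = 52.4 kg, so 7 ml/kg PBW = 367 ml.
- Actual weight = 32.5 × 1.60² = 83.2 kg.
- ABW = 52.4 + 0.25 × 30.8 = 60.1 kg, giving 421 ml, or 8.03 ml/kg PBW. With f = 0.40, ABW = 64.7 kg, giving 453 ml, or 8.64 ml/kg PBW.

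Tidal volume of 7 ml/kg ABW, expressed in ml/kg PBW (f = 0.25 / f = 0.40):

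| Patient | BMI 32.5 | BMI 35 | BMI 40 |
|---|---|---|---|
| Woman 160 cm | 8.03 / 8.64 | 8.24 / 8.99 | 8.67 / 9.67 |
| Woman 165 cm | 7.97 / 8.55 | 8.18 / 8.88 | 8.60 / 9.55 |
| Man 170 cm | 7.74 / 8.18 | 7.93 / 8.49 | 8.31 / 9.10 |
| Man 175 cm | 7.72 / 8.15 | 7.91 / 8.45 | 8.29 / 9.06 |

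- BMI 32.5: 7.72/7 = 1.10 to 8.64/7 = 1.23 (1.235 before rounding), so 10–24% more, or 49–88 ml.
- BMI 40: 8.29/7 = 1.18 to 9.67/7 = 1.38, so 18–38% more, or 87–145 ml.
- Above 8 ml/kg PBW with f = 0.25: 1 of 4 patients at BMI 32.5, 2 of 4 at BMI 35, 4 of 4 at BMI 40. With f = 0.40: all four at each BMI.

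**3. Size if it applies to the RM only.** The RM runs in pressure control, where volume = compliance × driving pressure. For the man of 170 cm at BMI 40, 462 ml (7 ml/kg PBW) needs a compliance of 462/20 = 23 to 462/15 = 31 ml/cmH2O. The ABW volumes, 549–601 ml, need 549/20 = 27 to 601/15 = 40. The ranges overlap, so the weight label does not fix the volume delivered in the RM. Both arms have the same maneuver in any case.

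**The case against.** The strongest reply is that the general settings and the iPEEP-group lines describe different phases: maintenance on PBW, the RM on ABW. The RM is common to both groups, so the arms would be treated alike and what remains is mostly untidy wording. A slip for "predicted" would likewise leave the arms equal. This stands as the likelier account. It does not remove the conflict, because no sentence shown limits ABW to the RM and the RM steps themselves name no basis. Figs 2–4 are not shown and might settle the scope.

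The lack of an ABW formula, and of an ABW entry in an abbreviation list that does have "PBW: Predicted body weight", is also no defect in a condensed article. That is accepted, and nothing here rests on it.

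A reader might infer that the iPEEP arm is in fact ventilated with larger breaths, or that most of its patients would exceed 8 ml/kg PBW. The protocol supports neither. The first needs the less likely reading. The second needs a BMI distribution, which the protocol does not give, and at f = 0.25 only one of the four example patients exceeds 8 ml/kg at BMI 32.5.

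Finally, tidal volume is already recorded every 5 minutes and respiratory parameters are a secondary endpoint, so an imbalance could be seen. That makes the remedy cheap; it does not correct the instruction.

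**Conclusion.** The point holds as a conflict in an operative ventilator instruction and should be fixed. That the text gives two unreconciled weight bases is certain. An effect on the trial is not shown: under the likelier readings the between-arm difference is zero. Only as a running setting in the iPEEP arm would nominal tidal volume be about 10–24% higher at BMI 32.5 and 18–38% higher at BMI 40. That range depends on the assumed PBW and ABW formulas, f of 0.25–0.40 and the four example heights. In that case volumes can pass the cited 6–8 ml/kg PBW range, and the comparison would mix tidal volume with PEEP.

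**What to change.** - State 7 ml/kg PBW as the single basis in both arms for titration and maintenance, and correct the line in the iPEEP-group steps accordingly.
- For the RM, either use PBW in the RM steps and the Fig. 2 legend, or say explicitly that ABW applies only to the RM and identically in both arms.
- Summarise delivered tidal volume in ml/kg PBW by arm from the 5-minute records, including the 36 patients already recruited. This would show which reading staff followed.
- Keep that summary descriptive. Delivered tidal volume arises after randomisation, so the arm comparison should not be adjusted for it.

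The cost is a wording correction and one descriptive table from data already collected. No model or sample size changes.

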**Fig. 3 Fig3:**
[figure not shown]
Individualized PEEP and perioperative management process. PEEP, positive end-expiratory pressure; iPEEP, individualized positive end-expiratory pressure; RM, the ventilator-driven alveolar recruitment maneuver; PEEP5, PEEP is 5 cmH_2_O

**Fig. 4 Fig4:**
[figure not shown]
Individualized PEEP titrated by optimal Cstat. Cstat, static lung compliance; PEEP, positive end-expiratory pressure; iPEEP, individualized positive end-expiratory pressure; RM, the ventilator-driven alveolar recruitment maneuver; PEEP5, PEEP is 5 cmH_2_O

### Study endpoints

The primary endpoints of this study are oxygenation index and proportion of lung collapse area.
Oxygenation index (PaO_2_/FiO_2_): At before induction (T0), after intubation (T1), after the last RM and before tracheal extubation (T3), and 20 min after extubation (T4), we draw arterial blood, perform blood gas analysis, and calculate oxygenation index.Proportion of lung collapse area: After all patients were admitted to the operating room, the first lung volume and its related parameters were measured using Drager’s EIT instrument. Two hours after surgery, EIT was performed again to measure the proportion of the area occupied by the non-ventilated lung tissue and calculate the proportion of its lung collapse area.

Secondary clinical endpoints include the following: blood gas analysis indicators, respiratory parameters, anesthesia-related parameters, inflammatory factors, incidence of PCCs, and health economic indicators.
Blood gas analysis parameters: At before induction (T0), after intubation (T1), after the last RM and before tracheal extubation (T3), and 20 min after extubation (T4), we draw arterial blood and perform blood gas analysis.Respiratory parameters: *V*_*T*_, RR, Pplat, PEEP, and Ppeak during operation are recorded every 5 min.Inflammatory factors: 5 ml venous blood is taken before surgery, 1 day after surgery, and 3 days after surgery. The blood is centrifuged and frozen at once by professional clinical test staff in order to detect IL-6, TNF-α, and serum procalcitonin (PCT) concentration in future.Anesthesia-related parameters: Circulatory parameters, anesthetic dosage, recovery time, and occurrence of hypoxemia are recorded continuously.Postoperative follow-up-related respiratory function and health economic indicators: ICU stay, hospital stay, hospital costs, complications, and other adverse events were recorded.PPCs is defined as following:
Mild respiratory failure: PaO_2_ < 60 mmHg or SpO_2_ < 90%, effective for oxygen response of 2 L/min, except for low ventilation, at least 10 min under air inhalation.Moderate respiratory failure: PaO_2_ < 60 mmHg or SpO_2_ < 90%, effective only for oxygen response of > 2 L/min, except for low ventilation.Severe respiratory failure: requiring support of mechanical ventilation or invasive ventilation.ARDS: ARDS according to Berlin definition.Bronchospasm (newly detected expiratory wheezing treated with bronchodilators).New pulmonary infiltrative inflammation (confirmed by chest X-ray, but no other clinical signs).Pulmonary infection (new or progressive radiographic infiltrate plus at least two of the following: antibiotic treatment, tympanic temperature > 38 °C, leukocytosis or leukopenia [white blood cell count < 4000 cells/mm^3^ or > 12,000 cells/mm^3^], and/or purulent secretions).Aspiration pneumonitis (respiratory failure after the inhalation of regurgitated gastric contents).Pleural effusion (chest X-ray demonstrating blunting of the costophrenic angle, loss of the sharp silhouette of the ipsilateral hemidiaphragm in upright position, evidence of displacement of adjacent anatomical structures, or [in supine position] a hazy opacity in one hemithorax with preserved vascular shadows).Atelectasis (lung opacification with shift of the mediastinum, hilum, or hemidiaphragm toward the affected area, as well as compensatory overinflation in the adjacent nonatelectatic lung).Cardiopulmonary edema (clinical signs of congestion, including dyspnea, edema, rales, and jugular venous distention, with chest X-ray demonstrating increase in vascular markings and diffuse alveolar interstitial infiltrates).Pneumothorax (air in the pleural space with no vascular bed surrounding the visceral pleura).

One of the above conditions was defined as positive for PCCs.

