### Sample size calculations

The primary outcome measures of this study were oxygenation index (PaO_2_/FiO_2_) and the ratio of lung collapse area to normal lung tissue by preoperative and postoperative EIT. According to the literature report [10], the ratio of pulmonary collapse detected by EIT in obese patients with individualized peep (iPEEP) set by EIT compared with PEEP 5 cmH_2_O was 6.2 ± 4.1% vs. 10.8 ± 7.1%, with a significant difference (*P* = 0.017). We hypothesize that the Cstat-titrated iPEEP will improve the rate of postoperative lung collapse in obese patients, with a probability of *α* = 0.05 to allow for type 1 error, *β* = 0.1 to allow type 2 error, and power 0.90; according to the mean of two groups obtained in the literature, 35 cases are needed for each group by using the PASS 20.0 software. A final sample size of 40 per group accounts for a 10% dropout rate in case follow-up.

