### Statistical analysis

After the trial, the research team will work with medical statisticians to analyze the data. Statistical analysis will be based on intention to treat. SPSS 20.0 statistical software was used for analysis.

The most of the source data will be recorded onto the CRF; however, before data analyzing, the pattern of missing data will be evaluated. The analysis of the graphics and data obtained by the EIT machine will be conducted by a special computer expert familiar with machine principles.

All data distribution will be detected by Kolmogorov-Smirnov analysis. Normal distribution data will be represented by mean and standard deviation (SD), and skewed data will be represented by median (quartile range). Compared with the related samples, *t* test will be used for normal distribution data; Wilcoxon signed-rank test and Mann-Whitney *U* test will be used for skewed data. The difference in proportions will be evaluated using Fisher’s exact test and the risk ratio of the associated 95% confidence interval (CI). The data of VAS score, ICU days, hospitalization days, and hospitalization costs will be analyzed by chi-square test. *P* value < 0.05 will be considered significant.

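### Two endpoints are called primary and judged at one 0.05 threshold, but alpha and 90% power were computed for EIT lung collapse only, and how the two results combine is not stated

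*Protocol article*

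**What the plan says.** All places are in the protocol article.

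- **Study endpoints:** "The primary endpoints of this study are oxygenation index and proportion of lung collapse area". The oxygenation index is calculated from blood drawn before induction (T0), after intubation (T1), before extubation following the last recruitment manoeuvre (T3), and 20 minutes after extubation (T4). No time point is singled out. Collapse has one assessment after the intervention: "Two hours after surgery, EIT was performed again to measure the proportion of the area occupied by the non-ventilated lung tissue".
- **Abstract, Methods:** "Primary endpoints will be postoperative atelectasis measured by chest electrical impedance tomography (EIT) and intraoperative oxygen index". This calls oxygenation intraoperative, which fits neither T0 nor T4.
- **Sample size calculations:** both endpoints are again called primary, but the assumptions are for collapse only: 6.2 (SD 4.1)% against 10.8 (SD 7.1)%. The error rates are "0.05 to allow for type 1 error" and "0.1 to allow type 2 error, and power 0.90", and the result is "according to the mean of two groups obtained in the literature, 35 cases are needed for each group", raised to 40 for dropout. No oxygenation difference or SD appears.
- **Statistical analysis:** one threshold for everything, "value < 0.05 will be considered significant".
- **Discussion:** the opening paragraph describes the study as adequately powered for oxygenation index, collapsed area, inflammatory factors and pulmonary complications. The closing hypothesis joins better oxygenation and less atelectasis with an 'and'.

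**The concern.** The error rates in the article are those of a trial with one primary endpoint, yet the endpoint section describes a trial with two. Which rule joins the two results decides whether the trial is positive.

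If one significant result is enough, the trial has two chances at 0.05, or three if both post-titration oxygenation values count, and the stated 5% is exceeded. If both must be significant, 5% holds, but the 90% covers only one of the two conditions. If alpha is divided, 35 per group no longer gives 90% power even for collapse. Under none of these rules do the stated alpha, power and group size all describe the trial's primary conclusion.

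**Working it through.** **1. The plan's own figure.** The inputs from the Sample size calculations section are a difference of 10.8 − 6.2 = 4.6 points, SDs of 4.1 and 7.1, alpha 0.05 and power 0.90. Sidedness is not stated.

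- Root-mean-square SD = √((4.1² + 7.1²)/2) = √33.61 = 5.80.
- Normal approximation, two-sided: n = 2 × (1.960 + 1.282)² × 33.61 / 4.6² = 33.4, so 34 per group.
- Noncentral t, two-sided: 35 per group, with power 90.3% (unequal variances) or 90.5% (equal variances). One-sided, 28 to 29 would do.
- Dropout: 35/0.90 = 38.9, so 39. The planned 40 leaves 40 × 0.90 = 36 evaluable.

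The 35 is reproduced. It belongs to collapse alone, tested at the full two-sided 0.05.

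**2. Which oxygenation values can show an effect.** The Intervention section puts all patients on PEEP 5 after induction and starts titration at pneumoperitoneum. T0 and T1 come before that, so they are baseline values. T3 and T4 come after it, and of these only T3 is intraoperative. The realistic family is therefore collapse plus T3 (two tests), or collapse plus T3 and T4 (three tests).

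**3. If either endpoint suffices.** For k independent tests at 0.05, the familywise error with no true effect is 1 − 0.95^k. The documents give no correlation between the test statistics, so the values 0.5 and 0.9 are assumptions. Those columns come from simulating equally correlated normal statistics (1,000,000 draws).

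| Tests | Independent | Correlation 0.5 | Correlation 0.9 |
|---|---|---|---|
| 2 (collapse, T3) | 1 − 0.95² = 9.75% | 9.1% | 7.0% |
| 3 (collapse, T3, T4) | 1 − 0.95³ = 14.3% | 12.5% | 8.4% |

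**4. If both endpoints must succeed.** Type I error stays at or below 5% with each test at 0.05. Joint power cannot exceed the lower of the two powers, and the oxygenation power is unknown. As an illustration only, if oxygenation also had 90% power, joint power would lie between 1 − 0.10 − 0.10 = 80% and 90%.

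**5. If alpha were split 0.025/0.025.** Power for collapse falls to 84.2% with 35 per group, or 85.3% with 36. Restoring 90% takes 42 per group. With dropout, 42/0.90 = 46.7, so 47 per group and 94 in total, against 80 planned.

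**The case against.** **The analysis plan may settle it.** A statistical analysis plan is not shown, and an article condenses the full protocol. Silence on hierarchy or on the analysis time point would not by itself be a finding, and that part of the objection stands. What remains lies in the article's own statements: the alpha, threshold and sample size fit one primary endpoint while two are named, and the Discussion claims power for an endpoint that was never sized.

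**Inflation is not established.** A reader might infer that the trial simply fails to control its type I error. The documents do not support that. It is true only if either endpoint suffices, and the closing hypothesis in the Discussion joins the two with 'and'. That wording is not a formal success rule, but it means the inflation must be stated conditionally.

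**Four time points are not four tests.** A reader might also infer that oxygenation is tested separately at T0, T1, T3 and T4. With collapse that makes five tests and 22.6% if all are independent (1 − 0.95⁵). The article lists when blood is drawn. It does not say that each time point is tested, and T0 and T1 precede titration. That figure should not be used.

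**The family may be only two tests.** The abstract's word 'intraoperative' can be read as pointing to T3. That is fair, so the two-test row is the main figure. The 14.3% also treats two ratios from the same patient shortly before and after extubation as independent, so it is an upper end.

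**Other rules would also work.** Requiring both endpoints, or splitting alpha, controls error too. The fixed sequence is preferred because it alone keeps 5% together with the computed 90% for collapse at the planned size.

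**Conclusion.** The point holds as a mismatch inside the article: two primary endpoints, one threshold, and an alpha and power that belong to one of them. If either endpoint suffices, the false-positive risk is about 7% to 10% for two tests and 8% to 14% for three, over assumed correlations from 0.9 down to 0. If both must succeed, the 5% is safe, but the trial's power is unknown and cannot exceed that for collapse. The sample size arithmetic for collapse is correct. The Discussion's statement of adequate power for oxygenation has no support in the document. This bears on the primary conclusion and should be fixed before the analysis.

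**What to change.** Amend the protocol, and align the registry entry and any analysis plan:

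- Test EIT collapse at 2 hours after surgery first, at two-sided 0.05.
- Test the oxygenation index at T3 second, at two-sided 0.05, and only if collapse is significant.
- Treat T0 and T1 as baseline. Report T4 and all other comparisons as supportive, with confidence intervals.
- State that the 90% power applies to EIT collapse only, in both the Sample size calculations section and the Discussion.

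The Trial status section reports 36 participants recruited, and the Blinding section says those delivering the intervention are not blinded. The amendment should therefore be dated, give its reasons, and record that nobody looked at outcome data by arm.

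**Cost.** No extra patients are needed: 35 evaluable per group (40 with dropout) still gives 90% power for collapse, and familywise error across the two tests stays at 5%. The downside is that oxygenation moves from a primary endpoint to second in the sequence. A formal claim on it is lost if collapse is not significant, and it still has no stated power.

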This trial will verify the following hypothesis: individualized PEEP titrated by the best static lung compliance (Cstat), combined with other lung-protective ventilation strategies, compared with the conventional setting of PEEP, can reduce atelectasis and PPCs in obese patients at intermediate to severe risk for PPCs. Through evaluation of atelectasis and ventilation distribution by electrical impedance tomography (EIT) of obese patients before and after laparoscopic surgery, we confirm the effect of iPEEP on oxygenation and postoperative PPCs in obese patients. Meanwhile, we observe the changes of perioperative pulmonary inflammatory factors and other health indicators (length of stay, hospital costs), so as to confirm its effectiveness and significance of iPEEP in reducing postoperative pulmonary complications in obese patients.

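### Read literally, the PPC definition counts a new infiltrate with no clinical sign or with two or more infection items, but not one with a single sign such as fever alone

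*Protocol article*

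**What the plan says.** The PPC list in the protocol article (Methods/design, Study endpoints) has twelve conditions. Two concern an infiltrate on chest X-ray:

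- **Infiltrate condition:** "New pulmonary infiltrative inflammation (confirmed by chest X-ray, but no other clinical signs").
- **Infection condition:** "Pulmonary infection (new or progressive radiographic infiltrate plus at least two of the following". The items are "antibiotic treatment, tympanic temperature > 38 °C, leukocytosis or leukopenia" (with white cell limits) "and/or purulent secretions".

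The scoring rule closes the list: "One of the above conditions was defined as positive for PCCs". There is no residual category, and the article does not say what counts as a clinical sign.

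PPC incidence is a secondary endpoint: "Secondary clinical endpoints include the following: blood gas analysis indicators, respiratory parameters, anesthesia-related parameters, inflammatory factors, incidence of PCCs, and health economic indicators". It is also part of the hypothesis in the Background, that the intervention "can reduce atelectasis and PPCs in obese patients at intermediate to severe risk for PPCs".

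**The concern.** An any-one-of composite should not turn from positive to negative as a patient gets sicker. Here the mildest infiltrate, an X-ray finding with no sign, already counts, and so does an infiltrate with an infection picture. The step between them is not covered.

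The stake is the PPC count. An assessor who applies the text literally scores the single-sign patient negative. One who follows the presumed intent scores the same patient positive. The definition does not settle which is right, so the endpoint could be scored inconsistently between patients.

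**Working it through.** No figure in the plan bears on this point, so there is none to reproduce. The check is to score every combination of the four infection items against the two infiltrate conditions.

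**Inputs (all from Study endpoints).** The four items are antibiotic treatment, temperature above 38 °C, abnormal white cell count and purulent secretions. Each is present or absent, which gives 2^4 = 16 patterns. Assume a new infiltrate, no sign outside the four, and none of the other ten PPC conditions.

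**Rule.** Let k be the number of items present. The infection condition is met when k ≥ 2. The infiltrate condition is met when no clinical sign is present.

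| Items present (k) | Patterns | Positive, all four items read as signs | Positive, only fever and purulent secretions read as signs |
|---|---|---|---|
| 0 | 1 | 1 | 1 |
| 1 | 4 | 0 | 2 |
| 2 | 6 | 6 | 6 |
| 3 | 4 | 4 | 4 |
| 4 | 1 | 1 | 1 |
| Total | 16 | 12 | 14 |

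**Broad reading.** The score is positive at k = 0, negative at k = 1 and positive again from k = 2.

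**Narrow reading.** Antibiotics alone and abnormal white cell count alone become positive, because neither is then a clinical sign. Fever alone and purulent secretions alone stay negative, so the gap shrinks but does not close.

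**Signs outside the four.** The cardiopulmonary edema condition in the same list names rales and dyspnea among clinical signs. A new infiltrate with rales as the only sign fails the infiltrate condition, and rales do not count toward infection.

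**Progressive infiltrates.** The infection condition admits a new or progressive infiltrate; the infiltrate condition admits only a new one. A progressive infiltrate that is not new is therefore uncovered at k = 0 and k = 1, which is 1 + 4 = 5 of 16 patterns.

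**Other conditions.** Respiratory failure, ARDS, bronchospasm, aspiration pneumonitis, effusion, atelectasis, cardiopulmonary edema and pneumothorax all require findings beyond an infiltrate with one sign. They rescue a single-sign patient only if that patient also meets one of them.

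**After rewording.** If the infiltrate condition takes any new or progressive infiltrate that does not meet the infection criteria, k = 0 and k = 1 fall there and k ≥ 2 falls under infection. All 16 patterns are then positive.

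**The case against.** The best defence is that the two conditions stand side by side and are meant as infiltrate without an infection picture and infiltrate with one. The Blinding section says observers are blinded, and a sensible observer might score a single-sign infiltrate as positive. That is a fair account of the likely intent. It does not make the text say so: fever and purulent secretions are clinical signs on any ordinary reading, and the article gives thresholds and an explicit scoring rule. What stands is that the text *could* undercount if applied literally; nothing shows that it *does*.

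It is also fair that antibiotic treatment is a care decision and white cell count a laboratory value. Neither need be a clinical sign, so half of the single-item patterns depend on the reading.

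Two stronger readings are tempting, and the documents support neither.

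- *A sizeable share of infiltrate patients is lost.* If each item occurred independently with probability p, the share with exactly one would be 4p(1−p)^3: 29% at p = 0.1 and 42% at p = 0.25, the maximum. But the protocol gives no item frequencies. The items would be expected to occur together, which for the same frequencies can push the share toward zero. It would also be a share of infiltrate patients only, before the other PPC conditions are considered.
- *The rule biases the comparison, or could reverse it.* The definition is the same in both arms and observers are blinded. Nothing shows that the intervention moves patients between no, one and two signs. Neither the direction nor the size of any bias can be derived.

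**Conclusion.** The gap is real, and it survives either reading of clinical signs. A new infiltrate with fever alone or purulent secretions alone meets neither infiltrate condition; antibiotics alone or abnormal white cell count alone may or may not. Such a patient scores PPC-negative unless another condition is met, while a milder patient with no sign scores positive. This is a fault in the wording given, not a detail left to an analysis plan, since a plan that applied the definition faithfully would inherit it.

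Its size is unknown. The affected patients must have an infiltrate, exactly the wrong number of signs and no other listed condition. In a trial of 80, that could be none or very few. The effect on PPC incidence and on the difference between arms cannot be calculated from the documents. The primary endpoints (oxygenation index and collapsed lung area) are unaffected, as is the sample size, which rests on the latter. This is a minor correction, worth making because it is cheap and because PPCs are named in the hypothesis.

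**What to change.** Replace the infiltrate condition with: *new or progressive pulmonary infiltrate on chest X-ray not meeting the criteria for pulmonary infection*. The two conditions are then mutually exclusive and together cover every infiltrate, and clinical signs no longer needs a definition. Apply the wording to all patients, including the 36 reported as recruited under Trial status, before any unblinded look at outcomes, and record the date of the change.

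**Cost.** No new procedure is needed. The component becomes slightly broader than the published wording, and the report should say so. Study visits and data collection lists postoperative complications and adverse events without detail. For patients already recruited, the X-ray finding may therefore have to be checked in hospital records if the CRF holds only a summary entry. PPC status itself does not need the four items, because every such infiltrate then counts. They are needed only if infiltrate and infection are reported separately.
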